#### Generation of the allocation sequence of randomization

Fifty patients who have no preference for either of the two therapies (acupuncture or cupping) will be randomly allocated to either the cupping or the acupuncture group. We will use SAS 8.0 software to create the sequence of randomization [25], total number of cases is 50, number of groups is 2, distribution ratio of the two groups is 1:1.

This sequence of randomization will be contained in opaque sealed envelopes and kept by researcher A, who will be contacted by each practitioner to provide the allocation.

#### Blinding methods

As the comparisons in this trial are different, outcome assessors and statistical analysts will be blinded. Outcome assessors will not be involved in participant allocation or treatment and will not be permitted to ask participants about information on allocation or treatment.

### Participants

#### Diagnostic criteria of fibromyalgia

Fibromyalgia will be diagnosed based on criteria formulated by the American College of Rheumatology (ACR) [26]. Key symptoms will be chronic widespread musculoskeletal pain, which will be assessed using scores of a widespread pain index (WPI) and a symptom severity (SS) scale [26].

#### Inclusion criteria

1. Participants with fibromyalgia diagnosed based on ACR criteria;

2. Participants whose scores for pain intensity are more than 30 mm (measured by VAS);

3. Participants 20 through 60 years of age;

4. Participants who fully understand the research process and are willing to provide informed consent.

#### Exclusion criteria

1. Persons with general musculoskeletal pain due to non-fibromyalgia illness;

2. Persons with mental disorders or other serious organic diseases, such as organ failure;

3. Persons taking oral pain medication or undergoing other interventions for pain relief during the trial;

4. Pregnant or lactating women;

5. Persons currently participating in another clinical trial.

#### Approach for cases of dropout/lost to follow-up/need to screen

1. Dropout cases will be defined as enrolled participants who miss a treatment session or refuse treatment as scheduled. We will consider at least 80% of the planned recruitment (40 cases in each group) to provide sufficient data for analysis.

2. Lost to follow-up will be defined as participants who complete all treatments, but cannot be contacted for follow-up.

3. Need to screen will be defined as enrolled participants who have serious adverse events during the trial. Researchers will be expected to halt treatment immediately and note the reason for the adverse event.

### Interventions

#### Cupping group (randomized and non-randomized)

Cups: Glass cups of three sizes will be used: large, 7 cm (edge diameter) × 9 cm (bore diameter) × 7.5 cm (height); medium, 6 cm × 8 cm × 6 cm; small, 6 cm × 7 cm × 5.3 cm. Jar size will be chosen based on treatment site.

Acupoints: *Ashi* (tender) points will be selected as the primary acupoints for flash cupping and retained cupping. Bladder channel (BL) and/or Du channel (DU) will be selected for moving cupping.

Cupping method: Retained cupping will be applied as the primary cupping method, supplemented with flash cupping and/or moving cupping. The procedure will be as follows. Suction (vacuum) will be created in the cups using flaming heat. Cups will then be applied immediately to acupoints on the BL and/or DU channels. Cups will be moved back and forth along the channel(s) several times. After cups are removed, flaming heat will be used to again create vacuum in the cups, which will then be applied to target treatment sites and retained for 10 minutes during each session. Treatment will be once daily, every other day, three sessions per week for five weeks.

#### Acupuncture group (randomized and non-randomized)

Needles: Stainless steel disposable needles (Wujiang Cloud Dragon Medical Instrument Company, Ltd., Jiangsu, China) of three lengths will be used, depending on the depth of the acupoint site: 0.25 mm × 25 mm, 0.25 mm × 40 mm, and 0.30 mm × 75 mm.

Acupoints: *Ashi*acupoints will be selected.

Acupuncture procedure: The skin at the acupoints will be disinfected. Needles will be inserted and manipulated for 15 seconds. Needle manipulation will be accomplished by using a twirling and up and down movement. Needles will be retained for 30 minutes each session. Treatment will be once daily, every other day, three sessions per week for five weeks.

#### Other allowable interventions

Patients will be permitted to take analgesics for pain relief during the follow-up period. Researchers will be expected to note the names, times, and doses of such medications.

### Outcome measures

#### Primary outcome

1. Patient adherence: Participant dropout,participants lost to follow-up, and reasons will be recorded (Table 1).

**Table 1 T1:** Schedule for treatment and outcome measurement

**Item**	**Screening**	**Treatment**															**Follow-up**		
**Session**	**1 (baseline)**	**2**	**3**	**4**	**5**	**6**	**7**	**8**	**9**	**10**	**11**	**12**	**13**	**14**	**15**	**16**	**17 (+1 m)**	**18 (+2 m)**	**19 (+3 m)**
Eligibility screening	√																		
Informed consent	√																		
Patient preference screening	√																		
Allocation	√																		
Patient expectation toward treatment	√																		
Treatment		√	√	√	√	√	√	√	√	√	√	√	√	√	√	√			
Widespread pain index	√					√					√					√	√	√	√
Symptom severity	√					√					√					√	√	√	√
Visual analogue score	√					√					√					√	√	√	√
Fibromyalgia intensive questionnaire	√															√	√	√	√
Hamilton depression scale	√															√	√	√	√
SF-36 Health survey	√															√	√	√	√
Patient satisfaction of treatment																√			
Number of dropouts or lost to follow-up																√			√
Practitioner attitude toward research model																√			√
Recording of adverse events	√	√	√	√	√	√	√	√	√	√	√	√	√	√	√	√	√	√	√

2. Patient satisfaction for the treatment: Patient satisfaction will be assessed at week 5 (Table 1). Satisfaction will be measured using a seven-score scale, with 1 for “very satisfied” and 7 for “very dissatisfied”.

3. Practitioner attitude for the research model: Individual or focus group interviews will be conducted after the trial (Table 1). All practitioners in the study (acupuncturists and cupping therapy practitioners) will be interviewed for their disposition toward conducting the PRPP trial model and their thoughts on this model compared with traditional randomized controlled trials.

#### Secondary outcomes

1. Adverse events: Adverse events will be observed during the five weeks of treatment and three months follow-up (Table 1). Researchers will be expected to note minor and serious adverse events that occur, including case ID number and symptoms.

2. Patient expectation for the treatment: Patient expectation will be assessed at week 0 (Table 1), measured by a four-score scale, with 1 for “symptoms totally disappeared” and 4 for “no change in symptoms”.

3. Visual analogue scale (VAS) [27] for pain intensity: The length of the VAS we will use is 100 mm, with “0” representing no pain and “100” representing unbearable pain that affects appetite and quality of sleep. Researchers will be expected to show the scale to patients and note the pain scores. VAS for pain will be measured once daily during week 0, at the end of every fifth treatment session (for a total of 15 assessments during the five-week treatment period), then during weeks 9, 13, and 17 of the follow-up period (Table 1).

#### Other outcomes

1. Widespread pain index (WPI) for pain intensity: The WPI is defined based on the ACR diagnostic criteria for fibromyalgia [26]. The WPI will be measured once daily during week 0, at the end of every fifth treatment session (for a total of 15 assessments during the five-week treatment period), then during weeks 9, 13, and 17 of the follow-up period (Table 1).

2. Symptom severity (SS) for pain intensity: SS is defined based on the ACR diagnostic criteria [26] for fibromyalgia. SS will be measured once daily during week 0, at the end of every fifth treatment session (for a total of 15 assessments during the five-week treatment period), then during weeks 9, 13, and 17 of the follow-up period (Table 1).

3. Hamilton Depression Scale (HAMD; Chinese translation) for depression [28]: The HAMD will be implemented three times at weeks 0, 5, and 17 (Table 1).

4. Quality of life measured by the SF-36 Health Survey (Chinese translation) [29]: The SF-36 will be implemented three times, at weeks 0, 5, and 17 (Table 1).

5. Revised Fibromyalgia Impact Questionnaire (FIQR, Chinese translation) for pain intensity [30]: The FIQR will be implemented three times, at weeks 0, 5, and 17 (Table 1).

### Data handling and statistical analysis

#### Data collection

A case report form (CRF) for each enrolled participant, listing demographic characteristics and baseline symptom spectrum, data outcome at each visit (Table 1), adverse events, and analgesic use, will be completed by outcome assessors at each visit.

#### Data management

EpiData Software (version 3.0.2, The EpiData Association, Odense, Denmark) will be employed for data management. Data from CRFs will be entered and stored by two data entry staff members. Data entry accuracy will be ensured using the double entry method.

#### Statistical analysis

To evaluate the feasibility of the PRPP model, we will use the chi-square, Cochran-Mantel-Haenszel (CMH)-chi-square, or Fisher’s exact test (as appropriate) to compare patient adherence and satisfaction toward treatment between groups and qualitative research methods to analyze patient and practitioner attitudes.

To assess the therapeutic effect of acupuncture and cupping therapy for fibromyalgia, we will use the chi-square, CMH-chi-square, or Fisher’s exact test (as appropriate) to compare baseline characteristics for categorical data. Analysis of variance (normal distribution) or non-parametric tests (skewed distribution) will compare baseline characteristics for continuous data. Analysis of primary outcomes will involve contrast analysis in which cupping therapy will be compared with acupuncture. This will indicate whether or not cupping and acupuncture differ in efficacy. This analysis will be conducted using repeat measurements in which outcomes will be compared at each follow-up, controlling for baseline scores. Intention-to-treat analysis[31] will be used in which missing data will be supplemented using the value that was assessed at the prior session (for example, if participant drops out at treatment session 6, then all outcome data would be noted as values at session 5). All calculations will be performed using SPSS for Windows (version 17.0, Chicago, Illinois), and *P*-values under .05 will be considered significant.

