### Objectives

The objectives of this trial are to assess the feasibility of applying the PRPP trial model in evaluating the therapeutic effect of acupuncture versus cupping, and to observe and compare the efficacies of these two therapies for fibromyalgia.

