#### Estimate of sample size

The first aim of this trial will be to investigate the feasibility of applying the PRPP model to evaluate the therapeutic effect of TCM non-drug therapy. The primary outcomes will be participant adherence and satisfaction. As a feasibility study, there is no previous study that provides relative data for us to use to calculate sample size.

The second aim of this trial will be to observe the therapeutic effect of the two types of TCM non-drug therapies of acupuncture and cupping for fibromyalgia with an equivalent test hypothesis. For this objective, the outcome will be pain relief, which will be measured by the VAS. We have used G*Power (version 3.1.2) to calculate the sample size.The analysis of variance (ANOVA) repeated measures technique was used as the statistical method during sample size calculation and will also be used for data analysis. To estimate the effect of cupping, we used data from our previous study [22], in which cupping produced a decrease in pain of 12.78 (SD = 5.88) points on the 100-mm VAS. We also used data from a trial on acupuncture for fibromyalgia [24] to estimate changes in pain that might occur in the acupuncture group. This corresponded to an estimated effect size of .2875. Using a two-tailed test with an alpha rate of .05, this meant that 38 participants are required per group to achieve 80% statistical power. Thus, we will aim for a total of 76 participants in two groups. Allowing for a dropout of 15%, we will recruit a total of 100 participants.

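### The quantitative feasibility analysis rests on between-group tests of adherence and satisfaction, which do not show whether adherence is high enough and have low power for moderate differences

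*Protocol article*

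**What the plan says.** The Objectives section puts feasibility first: the trial is to "assess the feasibility of applying the PRPP trial model in evaluating the therapeutic effect of acupuncture versus cupping". The section on sample size repeats this ("The first aim of this trial will be to investigate the feasibility of applying the PRPP model to evaluate the therapeutic effect of TCM non-drug"), adds "The primary outcomes will be participant adherence and satisfaction", and explains why no sample size was calculated for this aim: "As a feasibility study, there is no previous study that provides relative data for us to use to calculate sample size". Under Outcome measures, practitioner attitude to the research model is a third primary outcome.

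The Statistical analysis section fixes the method: "To evaluate the feasibility of the PRPP model, we will use the chi-square", the CMH chi-square or Fisher's exact test, as appropriate, "to compare patient adherence and satisfaction toward treatment between groups". The same sentence adds qualitative analysis of patient and practitioner attitudes. P-values below .05 count as significant.

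Two figures about retention stand elsewhere. The sample-size section has "Allowing for a dropout of 15%, we will recruit a total of 100 participants". The section on dropout has "We will consider at least 80% of the planned recruitment (40 cases in each group) to provide sufficient data for analysis". That section also counts a participant who misses a treatment session as a dropout.

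**The concern.** Whether a trial model is workable is largely a question of level: how many participants complete treatment and follow-up. A test between groups addresses a different question. Equally poor retention everywhere produces no difference, and a significant difference does not make the model unworkable. The same holds for satisfaction, since uniformly dissatisfied groups would also not differ.

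The comparison does have a use, because it can show whether preference affects adherence. But nothing was sized for that purpose, and the groups are small. The quantitative evidence for the first aim would then be a P-value that says nothing about the level of adherence and is often uninformative about a moderate difference.

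**Working it through.** **The plan's own figure.** There is none for this aim. The total of 100 comes from the pain (VAS) aim: 38 per group, 76 in all, with a 15% allowance. That step gives 76 / (1 − 0.15) = 89.4, so 90. Recruiting 100 implies an allowance of 1 − 76/100 = 24%. This does not drive the point, but it shows that the 15% is a loose planning figure.

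**Inputs from the article.**
- Cohorts: 50 without a preference and 50 with a preference (Abstract, Methods).
- Randomised arms: 50 allocated 1:1, so 25 each (randomisation section).
- Threshold: P < .05 (Statistical analysis).
- Reference figures: 15% dropout (sample size); at least 80% retained (dropout section), which allows a loss of 20%.

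**Assumed.** All dropout rates compared below are assumptions. The article gives only the 15% allowance.

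**Step 1: what the test shows when retention is uniformly poor.** Let each cohort of 50 lose 40%, twice the 20% loss that the dropout section still regards as leaving enough data. The rejection probability is the sum, over all pairs of dropout counts (i, j) with P < .05, of Bin(i; 50, 0.40) × Bin(j; 50, 0.40).
- Uncorrected chi-square: 5.2%, so non-significant about 95% of the time.
- Fisher: 3.2%, so non-significant about 97% of the time.

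This is the test's error rate under equal proportions, as it must be: the result carries no information on the level. At exactly 25/50 dropouts in each cohort, chi-square gives P = 1.0.

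**Step 2: power when the groups do differ.** The same enumeration with unequal rates gives:

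| Assumed dropout | 25 v 25: Fisher | 25 v 25: chi-square | 50 v 50: Fisher | 50 v 50: chi-square |
|---|---|---|---|---|
| 15% v 5% | 7% | 21% | 24% | 39% |
| 15% v 25% | 8% | 15% | 17% | 24% |
| 15% v 30% | 15% | 26% | 35% | 44% |
| 10% v 25% | 18% | 30% | 41% | 53% |
| 5% v 25% | 37% | 56% | 75% | 85% |

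Which test would apply depends on the expected dropout count per group, n × (p1 + p2)/2. For 10% v 25% this is 50 × 0.175 = 8.75 at 50 per group, where chi-square would ordinarily be used. At 25 per group it is 25 × 0.175 = 4.4, where Fisher would be. With 15% as reference, the normal approximation reaches 80% power only at about 40% dropout in the other group (50 per group) or about 51.5% (25 per group).

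**Step 3: what estimation gives from the same data.** Exact (Clopper-Pearson) 95% limits for x dropouts of n are Beta(0.025; x, n − x + 1) and Beta(0.975; x + 1, n − x).
- 15/100: 8.6% to 23.5%.
- 8/50: 7.2% to 29.1%.
- 40/100: 30.3% to 50.3%.

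The last line is the situation of Step 1. The interval lies wholly above a 20% loss, so the poor retention is plain where the test would usually report no difference.

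**The case against.** Four points can be made for the plan, and each limits the claim.

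1. **The tests are not the sole basis for feasibility.** A reader might infer that the first aim will be decided by adherence P-values. The document does not support that. The same sentence covers satisfaction and adds qualitative work, practitioner interviews are a primary outcome, and dropouts are recorded with reasons. No rule equates non-significance with feasibility.

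2. **The comparison has a purpose.** The Background motivates the design by the dropout that preference can cause in conventional trials, and the Study design section names comparison of participants with and without a preference as a strength. Comparing adherence between cohorts is therefore relevant. It still does not establish that adherence is adequate.

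3. **Power is not low throughout.** A reader might infer that a retention advantage in the preference cohort would probably be missed whatever its size. That fails for 5% v 25% at 50 v 50 (75% or 85%). It holds for smaller gaps. The article is also open that no sample size could be calculated for this aim.

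4. **The 15% and 80% are not feasibility criteria.** A reader might take them as benchmarks already in the plan. The first is a sample-size allowance for the pain outcome, and the second concerns sufficient data for analysis. Since one missed session among 15 counts as dropout, the recorded rate could be well above the rate of stopping treatment, and setting it against 15% or 20% could mislead.

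It may also be said that confidence intervals are a reporting detail for an analysis plan that is not shown. But the article does not leave the method open: it names significance tests for the first aim, and that choice is what is questioned.

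**Conclusion.** The point holds in limited form. The stated quantitative method for the first aim cannot show whether adherence is high enough for the model to be workable. This is a matter of logic and needs no assumed rates.

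The statement on power does rest on assumed rates and the planned group sizes. Differences of 10 to 15 points are more likely than not to be missed at 25 v 25, and are detected with at best about even odds at 50 v 50. A gap of 20 points from a low base is likely to be found at 50 v 50. The split of the preference cohort between treatments is not fixed, so contrasts within it could be weaker still.

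This is a change the sponsor should make. It does not undermine the trial, because the data needed are already collected and other evidence on feasibility is planned.

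**What to change.** In the Statistical analysis section:

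- Make the main quantitative feasibility analysis the estimated proportions of dropout and of loss to follow-up, with exact 95% CIs, overall and for the randomised and preference cohorts separately.
- Add the randomised-minus-preference difference with its 95% CI.
- Keep the chi-square, CMH or Fisher tests as descriptive, and keep the qualitative analysis as planned.
- Show the 15% allowance and the 80% figure as reference values only, unless the sponsor explicitly adopts them as feasibility criteria.
- Report missing any session (the current dropout definition) separately from stopping treatment, so that the two are not read as one rate.

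The cost is wording only, with no new participants or visits; the split in the last item uses session attendance. The small downside is that the statement on feasibility becomes tied to an observed level, which may be unfavourable.

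### The test list for the seven-level satisfaction score, a primary outcome, does not fix a method that uses the ordering of the scale

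*Protocol article*

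**What the plan says.** All references are to the protocol article.

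- Estimate of sample size, on the feasibility aim: "The primary outcomes will be participant adherence and satisfaction". No effect size, power or sample size is given for either outcome; the authors say that no earlier data were available.
- Primary outcome, item 2: "Satisfaction will be measured using a seven-score scale", running from the most satisfied answer at 1 to the least satisfied at 7. It is measured once: "Patient satisfaction will be assessed at week 5 (Table 1").
- Statistical analysis, first paragraph: "we will use the chi-square, Cochran-Mantel-Haenszel (CMH)-chi-square, or Fisher’s exact test (as appropriate"). The same sentence applies the list jointly to adherence and satisfaction: "exact test (as appropriate) to compare patient adherence and satisfaction toward treatment between groups". The section does not say when each test applies, which CMH statistic is meant, or whether the seven levels will be collapsed.
- Statistical analysis, second paragraph: rank-type methods appear only for skewed baseline variables, where "non-parametric tests (skewed distribution) will compare baseline characteristics for continuous data".
- The significance level is 0.05: "values under .05 will be considered significant".

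**The concern.** One list of tests serves two different kinds of data. Adherence is binary, and chi-square or Fisher suits it. Satisfaction is ordered. An order-blind test of a 2 x 7 table looks for any difference in pattern on 6 degrees of freedom. The natural question, whether one group is more satisfied than the other, needs 1.

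The repeated-measures analysis described later in the section cannot cover satisfaction, which has one assessment and no baseline value. The shared list is therefore the only between-group test stated for it.

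At stake is the chance of detecting a real shift in satisfaction between modalities, or between the preference and randomised cohorts, in a trial not sized for this outcome. Leaving the test open also allows analyses of quite different power for one primary outcome.

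**Working it through.** **The plan's own figure.** The only calculated sample size is for the VAS objective: effect size 0.2875, 38 per group, 76 in total, 80% power, with "Using a two-tailed test with an alpha rate of .05". For a two-group repeated-measures ANOVA (between-groups effect), the noncentrality is f²·N·m / (1 + (m − 1)ρ). With f = 0.2875, m = 4 measurements and ρ = 0.7, this gives N = 76; m = 2 and ρ = 0.5 gives 74. The article states neither m nor ρ. The figure is reproducible under plausible choices but says nothing about satisfaction.

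**How sparse the table is.** The randomised cohort is 50 patients at 1:1, so 25 per arm. Seven levels by two arms is 14 cells, and 50/14 = 3.6 patients per cell on average. With equal arms, the expected count in a cell is half its column total, so it falls below 5 when fewer than 10 patients in all choose that level. With six or seven levels in use, at most four columns can hold 10 or more of the 50 patients. Then at least 2 of 6 (33%) or 3 of 7 (43%) of the expected counts are below 5.

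**Where a cell-count rule would lead.** Assume Fisher when more than 20% of expected counts are below 5, otherwise Pearson chi-square. In simulation at 25 per arm, at least 99.7% of tables met the condition for Fisher. At 50 per group it was 96–99% for uneven score distributions, and 7–64% when the reference group's scores were uniform; the rest go to Pearson. Both tests ignore the ordering.

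**Power lost.** Inputs: two-sided 0.05, 2000 simulated trials per scenario, a proportional-odds shift, and three assumed reference distributions (uniform, moderately uneven, skewed). The 50-per-group case fits the randomised v preference comparison (50 v 50), or the two modalities pooled if preferences split evenly. Entries are power in percent, cell-count rule / Wilcoxon:

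| Per group | Odds ratio | Uniform | Moderate | Skewed |
|---|---|---|---|---|
| 25 | 2 | 12.6 / 25.8 | 12.9 / 27.5 | 14.2 / 25.6 |
| 25 | 2.5 | 19.6 / 41.6 | 22.9 / 44.9 | 25.0 / 41.9 |
| 25 | 3 | 30.9 / 61.2 | 30.7 / 56.4 | 32.8 / 54.9 |
| 25 | 4 | 47.8 / 77.4 | 48.0 / 77.6 | 47.8 / 72.1 |
| 50 | 2 | 23.2 / 50.0 | 26.2 / 49.8 | 26.6 / 47.9 |
| 50 | 2.5 | 42.1 / 73.2 | 43.6 / 74.4 | 43.7 / 69.7 |
| 50 | 3 | 60.0 / 86.8 | 57.8 / 84.2 | 60.6 / 84.2 |
| 50 | 4 | 81.6 / 96.9 | 83.2 / 96.6 | 82.3 / 94.9 |

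At 25 per arm the loss runs from 25.6 − 14.2 = 11.4 points to 61.2 − 30.9 = 30.3 points. At 50 per group it runs from 94.9 − 82.3 = 12.6 to 73.2 − 42.1 = 31.1 points.

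**Sample-size equivalent.** At 80% power and 0.05, the required noncentrality is 13.62 on 6 df and 7.85 on 1 df. The ratio 13.62/7.85 is about 1.7: for a purely directional shift, an order-blind test needs about 1.7 times as many patients.

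**Type I error.** With no true difference, rejection rates were 3.2–5.0% (Pearson), 4.2–5.2% (Fisher) and 4.2–5.6% (Wilcoxon). All are near or below 5%.

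**The CMH option.** The mean-score form with rank scores matches Wilcoxon. With integer scores it had at most about 7 points less power in these scenarios. The general-association form ignores the ordering.

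**The case against.** A reader might infer that the plan commits satisfaction to an order-blind test. The article does not support that. It states no expected-count rule; its qualifier could equally mean that the test is matched to the type of data. One of the three listed tests, CMH, has a form that uses the ordering fully, so the plan already permits the remedy. This stands, and it limits the point to a choice left unfixed.

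It can also be said that the form of CMH is a detail for the statistical analysis plan, which is not shown. That would carry more weight had the article left the analysis open. Instead it names the tests, and two of the three suit an ordered outcome poorly.

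The size of the loss rests on assumed distributions and on proportional odds, which favours a rank test. A difference in spread or shape, not direction, would shrink or reverse it. This stands too.

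Finally, the better test does not cure small numbers. At 25 per arm and an odds ratio of 2.5, it still has only 42–45% power. That is true, but no reason to give up more.

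**Conclusion.** The point holds as a cheap improvement. The article gives an ordered seven-level primary outcome the test list used for binary data and does not fix the one listed form that uses the ordering. If expected cell counts decide the test, the analysis will be order-blind, with a loss of about 11 to 30 points of power at 25 per arm and 13 to 31 points at 50 per group for odds ratios of 2 to 4. Those figures depend on the assumed selection rule, score distributions and proportional odds; the article gives no satisfaction data to replace them.

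Two stronger conclusions should not be drawn. The results would not be invalid, because type I error is held. Nor can it be said that real differences will be missed, because the article neither selects an order-blind test nor claims any power for satisfaction.

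**What to change.** In the Statistical analysis section, separate the two outcomes. For satisfaction, name the Wilcoxon-Mann-Whitney test (equivalently the CMH row-mean-score test with rank scores), stratified by cohort (randomised v preference) when the cohorts are pooled. Keep chi-square or Fisher's exact test for binary adherence.

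A proportional-odds model giving an odds ratio and 95% confidence interval is an optional addition. It should not be the main analysis, because it may be unstable with sparse cells.

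The cost is one sentence, with no new data, visits or patients. The one small loss is sensitivity to differences that are not a shift in one direction.

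### The analysis labelled as that of the primary outcomes fits none of the declared primary outcomes; it is most plausibly the VAS analysis, and it has no single decisive test

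*Protocol article*

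**What the plan says.** Two sections name the primary outcomes, and they differ. Under Estimate of sample size: "The primary outcomes will be participant adherence and satisfaction". The list under Primary outcome has both of these and a third item: "Practitioner attitude for the research model: Individual or focus group interviews will be conducted after the trial". Adherence is described there as "Participant dropout,participants lost to follow-up, and reasons will be recorded"; satisfaction is a single rating at week 5.

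The Statistical analysis section has two parts. Its first paragraph covers feasibility: chi-square, Cochran-Mantel-Haenszel or Fisher tests for adherence and satisfaction, and qualitative methods for attitudes. Its second paragraph covers therapeutic effect. There, what it calls the analysis of primary outcomes is a contrast of cupping with acupuncture, meant to show whether they differ in efficacy, by "repeat measurements in which outcomes will be compared at each follow-up, controlling for baseline scores". P-values below .05 count as significant.

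The sample-size section gives pain relief on the VAS as the outcome for the efficacy aim. It says repeated-measures ANOVA was used for sizing and will be used for analysis. The outcome list places "Visual analogue scale (VAS) [27] for pain intensity" among the secondary outcomes.

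**The concern.** A model that controls for baseline scores needs an outcome with a baseline score. Dropout status, a satisfaction rating given after treatment and practitioner interviews have none. The label and the method therefore cannot both be right, and the reader has to guess which outcome the main contrast concerns.

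The guess matters because the recruitment target of 100 is built on the VAS comparison. As written, an outcome listed as secondary carries a primary label and is compared at several visits against the same threshold, with no visit or overall test named as decisive. Any one significant visit could then be presented as the primary efficacy result.

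**Working it through.** **1. Does the labelled analysis fit a declared primary outcome?** Measurement times are from Table 1.

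| Outcome | Declared as | Baseline score | Times | Analysis already given |
|---|---|---|---|---|
| Adherence (dropout, loss) | primary in both lists | no | sessions 16, 19 | chi-square type |
| Satisfaction | primary in both lists | no | session 16 | chi-square type |
| Practitioner attitude | primary in one list | no | sessions 16, 19 | qualitative |
| VAS pain | secondary | yes | baseline; sessions 6, 11, 16; 17, 18, 19 | repeated-measures ANOVA (sample-size section) |

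Only the last row fits a baseline-controlled repeated-measures efficacy contrast. WPI, symptom severity, FIQR, HAMD and SF-36 also have baseline and later values, so the choice of VAS is an inference. It rests on the sample-size section, which ties both the efficacy aim and the method to the VAS.

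**2. The plan's own figure.** The plan states 38 per group (76 in total), effect size .2875, two-sided .05 and 80% power. It does not state the number of measurements m, the correlation ρ or the type of effect size. Taking .2875 as f, the between-group test in a repeated-measures ANOVA has λ = f²·N·m / (1 + (m − 1)ρ) with 1 and N − 2 degrees of freedom. The required N is 76 for m = 4 or 5 with ρ = .7, and 74 for m = 2 with ρ = .5. Over m = 2 to 7 and ρ = 0 to .8, the within-subject and interaction tests need at most 50. So 76 is reachable but cannot be confirmed. Where it is reached, it is through one overall between-group test and not through separate visit tests.

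**3. Error rate if each visit is tested separately at .05.** With k independent tests and no true difference, the chance of at least one P < .05 is 1 − 0.95^k.

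- k = 3 (follow-up sessions 17–19): 1 − 0.95³ = 14.3%
- k = 6 (all post-baseline VAS visits in Table 1): 1 − 0.95⁶ = 26.5%

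Repeated VAS scores from one patient are correlated. Simulation of equally correlated normal test statistics (1,000,000 draws, assumed ρ) gives:

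| ρ | k = 3 | k = 6 |
|---|---|---|
| 0.3 | 13.6% | 24.1% |
| 0.5 | 12.5% | 20.7% |
| 0.7 | 10.9% | 16.5% |
| 0.8 | 9.9% | 13.9% |

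**4. The count of visits.** The VAS text under Secondary outcomes gives 15 treatment-period assessments, while Table 1 marks three. The same text sets an assessment after every fifth session, and 15 sessions / 5 = 3, which agrees with Table 1. The calculation uses Table 1, but the conflict should be corrected.

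**The case against.** The strongest reply is that this is a labelling slip with a recoverable meaning. The disputed sentence stands in the therapeutic-effect paragraph, and the sample-size section supplies both outcome and method. Time points and multiplicity for a secondary outcome of a feasibility study are commonly left to an analysis plan. Much of this stands, and it limits the point. What remains is that the protocol assigns the wrong label, gives two primary lists, and itself states comparison at each follow-up with a flat threshold. That is a rule as written, not an omitted detail.

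A reader might infer more than the text supports:

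- *That the declared primary outcomes have no analysis.* They do, in the first paragraph of the Statistical analysis section.
- *That none of them is recorded more than once.* Table 1 marks dropout and practitioner attitude at sessions 16 and 19. What all three lack is a baseline score.
- *That six separate tests are certain and the error rate is 26%.* The wording may mean only the three follow-up visits, or contrasts within one model. The 26% also needs independence, which is implausible here; carrying the last value forward raises the correlation further.
- *That this error rate applies whatever the hypothesis.* The sample-size section speaks of an equivalence hypothesis. The figures count false claims of difference, which is what the Statistical analysis section says the contrast is for.
- *That patients who use analgesics in follow-up would be dropped from the analysis.* One section says "Patients will be permitted to take analgesics for pain relief during the follow-up period", while an exclusion criterion names "Persons taking oral pain medication or undergoing other interventions for pain relief during the trial". These conflict in wording, but no text removes enrolled patients, and the analysis is by intention to treat.

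**Conclusion.** The contradiction holds on the document alone: two different primary lists, and an analysis labelled primary that fits neither. That it is meant for the VAS is a strong inference, not a stated fact.

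The size depends on how the visit comparisons are read. If visits are tested separately, the chance of a false claim of difference is roughly two to three times the nominal 5% for the three follow-up visits (about 10–14%). For six visits it is roughly three to five times (about 14–26%). The correlations are assumptions, and the upper ends assume independence. If a single overall group contrast was intended, 5% is held, but the text does not say so. The feasibility aim, which comes first, is not undermined. The point is worth correcting because the trial is sized on the VAS comparison.

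**What to change.** - Use one list of primary outcomes in Estimate of sample size, Primary outcome and Statistical analysis.
- Retitle the cupping-versus-acupuncture contrast as the analysis of VAS, the main efficacy (secondary) outcome.
- Before unblinding, fix one decisive test. It can be the single overall between-group contrast from the repeated-measures model, which matches the method used for sizing, or one named visit. Week 5 is a candidate, but nothing in the document makes it the only choice.
- Report individual visits as supportive estimates with confidence intervals. Beside follow-up VAS, show by group the analgesic use that the case report form already collects, since greater use in the worse arm would shrink a difference.
- Correct the count of treatment-period VAS assessments to agree with Table 1, or the reverse.
- Separately, the sponsor must reconcile exclusion item 3 with the section on other allowable interventions.

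No new data are needed. Individual visits lose confirmatory status, and the decisive test would be set while recruitment is under way. The two options also differ in power. If .2875 is f, a single visit has d = 2 × .2875 = .575, and 38 per group give about 70.8% power at .05 (normal approximation, no gain from baseline adjustment counted), against the 80% planned. The overall contrast stays closer to the sizing but averages over visits at which analgesic use may differ between groups.
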